### Trial assessments and follow-up

All willing patients will be assessed prior to randomisation to confirm full eligibility (table 1). Recruited participants will be assessed at various timepoints (table 2).

**Table 2 T2:** Trial schedule of assessment

	Early assessments			Treatment		Follow-up assessment (measured post start of CRT)					
	Eligibility	Baseline	Pretreatment	On treatment	End of treatment	2 weeks	3 months	6 months	9 months	12 months	24 months
Informed consent	X										
Histopathology	X										
Performance status	X		X		X	X	X	X	X	X	X
Blood	X		X	X	X						
Pregnancy screening	X										
ECG		X									
MRI (pelvis)	X						X	X	Local schedule		
CT (chest, abdomen, pelvis)	X						Local standard schedule				
Flexible sigmoidoscopy*	X						X	X		X	
Digital rectal examination	X						X	X	X	X	X
Clinical assessment	X			X	X		X	X	X	X	X
Toxicity (CTCAE)		X		X	X	X	X	X	X	X	X
PROMs		X			X		X	X	X	X	X

*Additional flexible sigmoidoscopy assessments may occur for monitoring according to local schedules

CRT, Chemoradiotherapy; CTCAE, Common Terminology Criteria for Adverse Events; PROM, patient-reported outcome measure.

For further detail of the participation flow, see trial schema (figure 1).

Adverse reactions (ARs), serious adverse reactions (SARs), related unexpected serious adverse events (RUSAEs) and serious adverse events of interest (SAEoI) will be collected from randomisation until the 24-month follow-up point. SAEoIs are events identified by the research team that need additional monitoring, including angina/myocardial infarction, pulmonary embolism, serious skin reactions.

Data will be collected from all randomised participants, irrespective of treatment compliance. Where possible, endpoint and PROMs data will be collected from withdrawn participants who do not withdraw consent from further data collection.

### Treatment and response assessment quality assurance

The trial will implement robust quality assurance (QA) of radiotherapy treatment and the primary endpoint assessments. The radiotherapy QA programme will be implemented by the National Radiotherapy Trials Quality Assurance Group to ensure treatment is planned and delivered according to the trial protocol. All radiotherapy centres will complete pretreatment benchmark exercises. Anonymised pretreatment, 3-month and 6-month endoscopic photographs and MRI scans will be collected for all patients, with the first two patients from each site reviewed centrally. Trial Management Group (TMG) specialist members will ensure the inclusion/exclusion criteria have been met (baseline scan) and response has been correctly reported (3 and 6 months), providing feedback where necessary. Further review may be performed in batches.

### Statistical analysis

A full statistical analysis plan will be written before any analyses are undertaken. No formal interim analyses are planned within the trial.

The primary endpoint will be assessed on a *modified intention-to-treat* (*MITT*) *population*; all randomised participants who have had at least one dose of trial treatment, grouped by the treatment arm to which they were randomised (regardless of ineligibility, non-compliance or withdrawal).^38^

A multivariable logistic regression model, adjusted for the minimisation factors, will be used to compare the proportion of participants achieving a cCR at 6 months. Significance testing will be one sided at the 20% level. The treatment effect will be presented as an OR with a two-sided 60% CI (equivalent to a one-sided 80% lower confidence limit). Patterns of missing data and imputation methods (including multiple imputation) will be explored, if appropriate. A sensitivity analysis will be performed using the alternative definition of cCR.

All secondary analyses will use a 5% significance level and a two-sided CI, where appropriate. Safety data will be presented on the *safety population*; participants are summarised on the treatment received regardless of randomisation. All other data will be summarised on an MITT population.

Summary statistics will be presented for toxicities on the number and proportion of participants experiencing ARs, SARs, RUSAEs and SAEoI. Treatment compliance to the allocated radiotherapy (±chemotherapy) will be monitored and presented, including summaries for delays, dose modifications and discontinuation. PROMs will be summarised and reported using standard guidelines.^32 39 40^ Repeated measures models will be used to assess differences between treatment arms. Cumulative incidence will be used to compare the time to stoma formation between treatment arms. Overall survival will be compared using the Cox proportional hazards model. Kaplan-Meier curves and survival estimates with corresponding CIs will also be presented.

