## Methods and analysis

### Design and aim

APHRODITE is a phase II, multicentre, open-label randomised controlled trial of IMRT, with select use of concomitant chemotherapy, in patients with early-stage rectal cancer (T1-3bN0, maximum diameter ≤4 cm) who are deemed not suitable for radical TME surgery by their multidisciplinary team (MDT). The primary aim is to assess whether radiotherapy dose escalation increases the cCR rate at 6 months from the start of CRT, compared with standard radiotherapy dose CRT, with acceptable toxicity. Patients may receive full dose, reduced dose or no concomitant chemotherapy. A total of 104 eligible patients will be recruited from 10 to 12 UK radiotherapy sites. Participants will be randomised on a 2:1 basis to receive escalated dose or standard dose chemoradiation. The participant pathway can be seen schematically in figure 1. The study protocol and this manuscript have been written in accordance with the Standard Protocol Items: Recommendations for Interventional Trials guidelines.

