### Trial objectives

The primary objective of APHRODITE is to compare the proportion of participants with a cCR at 6 months from the start of CRT. A composite definition for cCR is used, including digital rectal examination (DRE), rectal endoscopy and pelvic MRI, defined by:

No evidence of either mucosal tumour or submucosal swelling on white light endoscopy. A flat white scar remains, with or without telangiectasia.No palpable tumour on DRE.High-resolution pelvic MRI scanning shows either a linear scar only or dense fibrosis with no obvious tumour signal (mrTRG 1 or 2).^27 28^

This definition of cCR follows international consensus.^29^ Every effort will be made to ensure trimodality assessment (endoscopy, DRE and MRI). If such is not possible, confirmation should always include a rectal endoscopy and one other (DRE, MRI). Detailed guidance on MRI and endoscopy is provided in separate trial guidelines. The protocol does not require use of biopsy for response evaluation.

Currently research is unclear whether high-dose radiotherapy increases the rate of superficial mucosal ulcerations in the presence of a complete primary tumour response. Therefore, an alternative definition of the primary endpoint, with the inclusion of superficial mucosal ulceration classified as cCR, will be explored in a sensitivity analysis.

The secondary objectives of APHRODITE evaluate the safety and tolerability of dose escalation based on:

Acute toxicities as per Common Terminology Criteria for Adverse Events (CTCAE V.5.0) (measured weekly during and up to 2 weeks after end of treatment).Treatment compliance (both radiotherapy and, if received, concomitant chemotherapy).Toxicities during follow-up as per CTCAE V.5.0 (measured up to the 24-month follow-up point).

The longer term activity of dose escalation will be evaluated based on:

Time to stoma formation (time from randomisation to stoma formation—colostomy or ileostomy).Overall survival (time from randomisation to death from any cause).Patient-reported outcome measures (PROMs), assessed by the European Organisation for Research and Treatment of Cancer (EORTC) Quality of Life Questionnaires QLQ-C30^30^ and QLQ-CR29,^31^ low anterior resection syndrome (LARS) questionnaire^32^ and additional EORTC QLQ items from the Item Library relevant for organ preservation.

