### Randomisation and recruitment

A computer-generated minimisation programme incorporating a random element will be used to allocate patients on a 2:1 basis to receive escalated dose or standard dose chemoradiation, ensuring arms are well balanced for the following factors:

Randomising site.T-stage (<T3 vs T3).Chemotherapy use (either 100% or 75% dose) versus no chemotherapy use.

Randomisation will be performed centrally via the University of Leeds Clinical Trials Research Unit (CTRU) automated 24-hour randomisation system. The registration and randomisation process will be instigated by on-site research staff; patient consent form must be attained prior to registration (see online supplemental file 1).

10.1136/bmjopen-2021-049119.supp1Supplementary data

Recruitment will take place over 2 years, with an estimated monthly recruitment rate of four to six patients per month. APHRODITE opened in February 2020, with expected recruitment completion by winter 2022. The study has and will be presented at national and international meetings, increasing clinical awareness. A trial website and dedicated Twitter account will be used to further increase exposure, highlighting the trial population criteria to treating clinicians and MDT members. Based on preliminary feedback from clinicians and patient representatives in the study design phase, the 2:1 allocation between the intervention and control arms will make recruitment attractive for patients with limited standard treatment options.

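### Survival and time to stoma are dated from randomisation but analysed only in participants who start treatment, and no all-randomised analysis of cCR is stated

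*Protocol article*

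**What the plan says.** Four statements in the protocol article bear on this.

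- **Analysis set.** Statistical analysis defines the modified intention-to-treat (mITT) set for the primary endpoint as "all randomised participants who have had at least one dose of trial treatment, grouped by the treatment arm to which they were randomised". Ineligible, non-compliant and withdrawn participants stay in once treated. Safety is summarised by treatment received; for the rest, "All other data will be summarised on an MITT population". A reference is cited for the mITT set, but the text gives no reason for choosing it.
- **Time origins.** Trial objectives dates cCR from treatment ("compare the proportion of participants with a cCR at 6 months from the start of CRT") but survival from allocation ("Overall survival (time from randomisation to death from any cause"). Time to stoma formation is also counted from randomisation.
- **Knowledge of allocation.** Design and aim states: "APHRODITE is a phase II, multicentre, open-label randomised controlled trial of IMRT". Under Treatment regimen the arms have different planned tumour doses, so the arm is settled before the first fraction.
- **Data available.** Trial assessments and follow-up states: "Data will be collected from all randomised participants, irrespective of treatment compliance".

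The only sensitivity analysis firmly committed to concerns the endpoint definition: "A sensitivity analysis will be performed using the alternative definition of cCR". No analysis of all randomised participants is mentioned for any outcome.

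**The concern.** Whether a participant enters the analysis is decided after allocation is known. This has different consequences for the two kinds of endpoint.

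For survival and stoma, the clock starts at randomisation but the analysis set requires survival to the first dose. A death in that interval is an event under the endpoint's own definition and is then removed. So is a stoma formed in that interval if treatment is never given, and so is any later event in a never-starter. The population includes patients enrolled because of comorbidity or frailty, so early events are possible, although the article gives no rate.

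For cCR, dropping never-starters does no harm if they are few and balanced. If non-start differs by arm and is related to outcome, the treated groups are no longer the randomised groups. The Sample size section gives the direct comparison with a concurrent control as the protection against wrong decisions, and the test is one-sided at 20%, so a few participants can change the result.

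**Working it through.** **1. The plan's own figure.** Inputs from Sample size: 35% v 55%, one-sided 20%, 80% power, 2:1, continuity correction, 5% loss.

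- Average proportion: (0.35 + 2×0.55)/3 = 0.4833.
- Uncorrected control n = [0.8416·√(0.4833×0.5167×1.5) + 0.8416·√(0.35×0.65 + 0.55×0.45/2)]² / 0.2² = 25.70.
- With correction: (25.70/4)·[1 + √(1 + 3/(25.70×0.2))]² = 32.77.
- Total 3×32.77 = 98.3; 98.3/0.95 = 103.5, rounded up to 104.

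The stated 104 reproduces, so the sample size is not at issue.

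**2. How small a difference decides the trial.** Using 34 and 70 participants and no correction, the test turns positive at about 0.8416·√[p(1−p)(1/34 + 1/70)]. This is 8.4 points at p = 0.35 and 8.8 points at p = 0.45.

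**3. Effect of excluding never-starters on cCR.** The article gives no number of never-starters, so a range is assumed. Further assumptions: true cCR is 35% in all randomised participants of both arms, and never-starters have no cCR. With e experimental and c control never-starters, the treated rates are 0.35×70/(70−e) and 0.35×34/(34−c). The last column is the exact binomial probability that a one-sided 20% pooled z-test, unadjusted and without correction, is positive.

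| Never-starters (exp. / control) | Treated cCR (exp. / control) | Apparent difference | Type I error |
|---|---|---|---|
| 0 / 0 | 35.0% / 35.0% | 0 | 20.1% |
| 2 / 1 | 36.0% / 36.1% | 0.0 | 19.9% |
| 3 / 0 | 36.6% / 35.0% | +1.6 | 24.4% |
| 7 / 0 | 38.9% / 35.0% | +3.9 | 34.3% |
| 0 / 1 | 35.0% / 36.1% | −1.1 | 17.6% |
| 0 / 3 | 35.0% / 38.4% | −3.4 | 12.6% |

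Three never-starters are 4.3% of 70 or 8.8% of 34.

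**4. A single result near the line.** Control 12/34 (35.3%) v experimental 30/70 (42.9%) gives z = 0.737 and one-sided p = 0.230, which is negative at 20%. Dropping two experimental never-starters gives 30/68 (44.1%), z = 0.854 and p = 0.197, which is positive.

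**5. The reverse case.** Now let control participants of average prognosis refuse treatment, with true cCR 35% in both arms. Here mITT keeps its error rate, and scoring refusers as not cCR does not.

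| Control refusers | mITT | All randomised, refusers not cCR |
|---|---|---|
| 1 | 20.5% | 23.0% |
| 2 | 20.7% | 26.1% |
| 3 | 20.6% | 29.5% |

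**6. Survival and stoma.** No arithmetic applies. The definitions start at randomisation, the analysis set starts at first dose, and the interval between them is lost for anyone who never starts.

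**The case against.** The mITT set is defined openly, keeps participants in their allocated arm and retains everyone once treated. For cCR there is also a practical reason for it: the endpoint and the follow-up visits in Table 2 are timed from the start of chemoradiotherapy, so a never-starter has no scheduled 6-month assessment. Step 5 shows that an all-randomised analysis with never-starters scored as not cCR can itself favour the experimental arm. In a phase II trial seeking preliminary evidence of activity, the choice of primary cCR set is therefore a trade-off. All of this stands, and it argues against simply replacing the primary set. It does not help survival or time to stoma, which carry no such timing reason.

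Three stronger readings are tempting, and the article does not support them.

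- A reader might infer that the plan expects participants to prefer the intervention and so to leave the control arm. The sentence in question says "the 2:1 allocation between the intervention and control arms will make recruitment attractive for patients with limited standard treatment options". It concerns the appeal of the ratio before consent, and nothing in the article anticipates refusal after allocation.
- A reader might infer that participants who die before 6 months would be imputed a chance of cCR. The article says only that missing-data patterns and imputation methods will be explored if appropriate, and it defers to a full analysis plan. The handling of deaths is detail for that plan.
- A reader might conclude that the randomised comparison of cCR is broken. That needs non-start that is both unequal and prognostic, and the article gives no evidence of either.

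**Conclusion.** The point holds in two parts of different strength. For overall survival and time to stoma, the endpoint definitions and the analysis set contradict each other, and this holds whatever the number of never-starters. For cCR, the exclusion is a possible source of bias in either direction. Under the assumptions of step 3, the nominal 20% error moves to about 24% with three experimental-only never-starters and about 13% with three control-only, and stays near 20% when two experimental and one control fail to start. The figures rest on an assumed number of never-starters and an assumed outcome for them. They also come from an unadjusted test, so they only approximate the planned logistic model adjusted for the minimisation factors. The gap for cCR is that no all-randomised result is planned to set beside the mITT one.

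**What to change.** 1. Analyse overall survival and time to stoma in all randomised participants, by allocated arm.
2. Keep the mITT analysis of cCR and add a pre-specified analysis of all randomised participants with never-starters counted as not cCR. State in advance that the two are read side by side, because that scoring can favour the experimental arm if control participants refuse treatment.
3. Report the number of never-starters by arm, with reasons, so that a reader can judge which of the two results to trust if they differ.

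Scoring never-starters as not cCR removes the need for a 6-month date for them. Because the Table 2 visits run from the start of treatment, the plan should say when their survival and stoma status are recorded, counted from randomisation.

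The cost is a little more analysis work and slightly lower cCR rates in the added analysis. With equal non-start of 2%, 5% or 10% in both arms and no other loss, power with continuity correction is 80.4%, 78.8% or 76.2% on all 104 randomised, against 80.8%, 79.9% or 78.2% under mITT. That is 0.4 to 2.0 points, and no change to the sample size is needed.

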### Trial organisation

Trial coordination, data management and statistical analysis will be directed and conducted by the trial-specific project team at the University of Leeds CTRU. Trial supervision will be established according to the principles of Good Clinical Practice and in line with the relevant Research Governance Framework within the UK and CTRU standard operating procedures.

### Data collection and management

Participating sites will record participant data on trial-specific case report forms and submit them to the CTRU. Participants will complete PROMs on the relevant paper questionnaire forms at the time of their clinic appointment. All trial data will be entered, validated and stored securely by CTRU. Missing and discrepant data will be flagged and additional data validations raised, as appropriate, from the CTRU data management team. Missing data (except PROMs) will be followed up until received, or confirmed as not available. Data items regarding consent, patient safety and the primary endpoint will be subject to manual priority checking.

Data will be stored securely at Leeds CTRU. Only CTRU will have access to the data, prior to analysis and release of trial results. On completion of the trial, data will be stored in the sponsor archiving facility for a minimum of 15 years. After the final trial results have been published, interested researchers may contact the TMG and CTRU to request access to relevant data. Any requests will be reviewed by the TMG.

### Trial monitoring

The TMG will provide ongoing clinical, practical and statistical advice on trial-related matters. The trial will be overseen by an independent Trial Steering Committee (TSC) and Data Monitoring and Ethics Committee (DMEC). The DMEC comprises two clinical oncologists and one statistician. They will review and monitor accumulating interim safety data and unblinded reports, at least annually. Their role is to protect the safety of the participants and maintain the research integrity of the study, advising the TSC on trial developments, including advice on trial continuation. A trial-specific DMEC charter has been developed in line with the Data Monitoring Committees: Lessons, Ethics Statistics Study Group (DAMOCLES) recommendations.^41 42^ The sponsor and TSC have ultimate oversight over the conduct and continuation of the trial.

### Sample collection

Pretreatment routine diagnostic formalin-fixed paraffin-embedded tumour biopsy tissue samples will be collected on all patients and sent to the University of Leeds for storage. Consent will be taken for their use in future translational research. The routine glass H&E stained slides used for diagnosis will be scanned to create a digital pathology resource for QA of the trial and support translational research, including research examining biomarkers of radiosensitivity and radioresistance.

## Ethics and dissemination

The trial obtained ethical approval from the North West Greater Manchester East Research Ethics Committee (reference number 19/NW/0565) and is registered in the ISRCTN registry. Confirmed by the UK Medicines and Healthcare products Regulatory Agency, APHRODITE is not a clinical trial of an investigational medicinal product (non-CTIMP). The trial is currently adhering to protocol version 3.0 (approved 12 May 2021).

The primary endpoint and early toxicity data will be analysed and reported when the last participant reaches 6 months after start of treatment. Further analyses will be conducted when all patients have reached 24 months of follow-up. The final trial publication will be written by the TMG, and will adhere to International Committee of Medical Journal Editors guidelines.

## Discussion

There is currently a lack of prospective trials of dedicated non-surgical management strategies in rectal cancer. It is therefore unclear whether increased radiotherapy dose may contribute to short-term tumour response, long-term local control and organ preservation. In particular, the lack of randomised data from the early-phase setting has made it difficult to elucidate whether the high response rates observed in phase II trials are due to patient selection or treatment. The APHRODITE trial will provide high-level evidence whether dose escalation increases the cCR rate when directly compared with standard dose. Further studies will be required to provide evidence for whether a higher radiotherapy dose can provide improved long-term local control without surgery.

Other ongoing studies are examining dedicated organ preservation strategies for early rectal cancer. The STAR-TREC phase III trial (ISRCTN14240288) randomises patients with early (T1-3bN0) cancer with a preference for organ preservation between short-course and long-course standard (chemo)radiotherapies, with the aim of non-surgical management or local excision only. Both trials remain complimentary: STAR-TREC uses standard radiotherapy in a patient population suitable for surgery, while APHRODITE will assess intensified treatment in an alternative patient group. Three other studies of radiotherapy dose escalation strategies for organ preservation are ongoing: the international phase III OPERA trial (Organ Preservation in Early Rectal Adenocarcinoma, NCT02505750) randomises patients between moderately dose-escalated CRT (54 Gy) and standard dose CRT (45 Gy), followed by Papillon contact X-ray therapy (90 Gy in three fractions); the MORPHEUS trial (More Organ Preservation: High dose rate brachytherapy versus External beam radiation therapy Multiticenter Study - A randomised phase III trial, NCT03051464) randomises patients between moderately dose-escalated CRT (54 Gy) and CRT (45 Gy), followed by brachytherapy (30 Gy in three fractions); and the Danish multicentre WW3 phase II trial (NCT04095299) randomises patients between dose-escalated CRT (62 Gy) and standard dose CRT (50.4 Gy). All these studies require suitability for surgery, and the first two depend on access to specialised treatment equipment. The APHRODITE study thus fills a clear research gap in the current international trial portfolio.

Studies of non-surgical management and organ preservation for rectal cancer have focused on clinical endpoints, for example, cCR rate, stoma rate and overall survival, as well as the clinicians’ interpretation of patient outcome. There is a paucity of toxicity data including PROMs following non-surgical management, particularly in a patient population usually excluded from clinical trials. The APHRODITE study will prospectively measure toxicity and PROMs, providing a valuable and unique data set.

At present, there is a lack of understanding of how patients weigh and prioritise different potential outcomes, including the balance between efficacy and toxicity, in the setting of non-surgical rectal cancer treatment. The decision regarding which severity of treatment-related toxicities is acceptable for a given organ preservation strategy has previously been evaluated purely by clinicians. Two small studies examined patient preferences for organ-preserving and surgical treatment approaches.^47 48^ However, no studies have focused specifically on patient attitudes to treatment characteristics and outcomes following non-surgical management. The APHRODITE patient preference substudy will help inform future dose escalation studies and help non-surgical management of rectal cancer to better reflect patient perspectives.

The APHRODITE trial will provide valuable, high-quality, patient-centred evidence for escalated dose radiotherapy in patients with rectal cancer not suitable for radical surgery, addressing an important research gap.
